#### D1 (means 24 hours after treatment with PZQ 24hs +/- 2 hours).

The physician in the research team will assess schoolchildren treated on D0 for adverse events using a questionnaire.

#### D21 (means 21 days after treatment +/- 2 days)

The physician in the research team will assess schoolchildren treated on D0 for adverse events using a questionnaire. In addition, Hb will be determined in all schoolchildren in the trial. Stool samples will be collected on two separate days and each day duplicate Kato Katz slides will be made for quantitative examination of *S mansoni* ova. This will allow cure rate and egg reduction rate at D21 to be calculated.

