## **3. EXPERIMENTAL DESIGN AND METHODS**

The trial described below will be conducted in compliance with the protocol, Good Clinical Practice and applicable regulatory requirements.

3.1. *Study site.* The study is to be done in Mwanza Region, Tanzania, where both *S. mansoni* and *S. haematobium* are highly endemic particularly in Magu and Misungwi districts. In a recent survey of schoolchildren by [name], *et al* (1999) in the area the prevalence of urinary schistosomiasis was found to be 56.5% (range 13.6-87.7%) and 10.9 % (range 0.0-64.4%) for intestinal schistosomiasis. *S. mansoni* is more prevalent along the Lake Victoria shore, while *S. haematobium* is more prevalent in the hinterland, away from the lakeshore. In this area mixed *S. haematobium/ S. mansoni* infections have a low prevalence of 4.0 % (range 0.0 – 21.0 %). The study will be done in schools reported by [name] *et al.* (1999) to have high prevalence of *S. mansoni*, i.e., Mayega 64.7%, Kigangama 53.3%, Lutale 49.5%, Kongolo 41.7%, Chumve 41.5%, Kabita 39.8%, Ihale 38.0% and Ilumwa 34.4%. Also schools located in the same area as the high prevalence schools may be considered for baseline screening. [name] (1988) have shown that peak transmission of *S. haematobium* in the area occurs during the short dry period, sometime in February/March so that most of the infections in the community would be detected in April/May. Magendantz (1972) showed that the transmission of *S. mansoni* occurs mainly in Lake Victoria throughout the year.

3.2. *Study design.* The proposed study is a double-blind, randomized controlled trial to determine if higher doses of praziquantel (PZQ 60mg/kg) will improve treatment efficacy of *S. mansoni* with an adequate safety profile, in comparison with standard regimen of PZQ 40mg/kg. The trial is to be conducted with schoolchildren aged between 10 to 19 years old. This age group is chosen because it is

school age children who are heavily infected by schistosomes, therefore, it is the group in which the new increased dosage of PZQ is anticipated to be used. The potential beneficiary of increased efficacy of PZQ is school-age children and, therefore, it would be prudent to determine the safety profile of the new dosage regimen in the same age group.

The following are the study endpoints:

- Primary endpoint:  
Cure rate at 21 days after treatment for the PZQ 60mg/Kg and PZQ 40mg/Kg groups.
- Secondary endpoints:

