#### D0 (means 7 days after baseline study +/-1 day)

Clinical history of each schoolchild fulfilling screening criteria using questionnaire will be taken to see if the subject has acute or chronic severe disease, including hepato-splenic schistosomiasis. In addition, the questionnaire will seek to establish a history of adverse reactions associated with PZQ, a history of treatment with PZQ within 30 days and medication (such as antibiotics) currently being used which may affect the results of the present trial. This will be followed by a thorough physical examination by a physician for physical fitness to participate in the trial. Those showing signs and symptoms of clinical malaria will be referred for treatment and excluded from the study and referred for treatment. Childbearing age female subjects will further be tested for pregnancy using the Quickstick™ One step HCG Pregnancy Test. Those tested positive for pregnancy will be excluded from the study. Each girl will be given individual counseling from the study nurse. Those children with schistosomiasis who will be excluded from the study at this point will be treated with a single oral dose of PZQ at 40mg/kg.

For the children who fulfill all criteria for enrolment, body weight will be determined and a finger-prick blood sample will be collected for Hb measurement. Thereafter they will be treated with PZQ according to weight and dosage regimen assigned in the trial (see randomization and blinding section for treatment assignment). During the 4 hours post-treatment study subjects will be observed for occurrence of adverse events and by the end of this period they will be assessed for adverse events using a questionnaire.

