#### 6.2.2. Stool:

At baseline and during follow-up visits each child in schools within 5 km of the Lake Victoria shore recruited in the study will provide a stool specimen on two separate days at maximum interval of 5 days. Duplicate Kato Katz slides (2 slides) (Katz et al., 1972) will be prepared in the field (using the 41.7mg faecal template) from each stool sample. The prepared Kato slides in the field will undergo quantitative microscopic examination for *S mansoni* ova.

Classification as egg count  $\geq 100$  eggs per gram of faeces for *S mansoni* will be obtained by the mean egg count for the 4 slides collected at baseline.

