### **7. ASSESSMENT OF EFFICACY:**

7.1. Parameter to be measured – egg count, as measured by the Kato-Katz method described above, at baseline, D21, 6M and 12M

The measurement of egg count for each time point will be estimated as the mean of the 4 slides collected (2 slides per sample, 2 samples within 5 days).

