### Baseline Screening, Treatment and Safety Assessment Schedule:

| Calendar | Day  | No. of subjects Screened | No. Kato Slides Made | Urine samples screened | Stool microscopy | Computer Data entry | D0  | D1  | D21 |
|----------|------|--------------------------|----------------------|------------------------|------------------|---------------------|-----|-----|-----|
| 1        | Mon  | 100                      | 200                  | 100                    |                  |                     |     |     |     |
| 2        | Tue  |                          | 200                  | 100                    | 200              |                     |     |     |     |
| 3        | Wed  | 100                      | 200                  | 100                    | 200              | Xx                  |     |     |     |
| 4        | Thur |                          | 200                  | 100                    | 200              | Xx                  |     |     |     |
| 5        | Fri  | 100                      | 200                  | 100                    | 200              | Xx                  |     |     |     |
| 6        | Sat  |                          |                      |                        |                  |                     |     |     |     |
| 7        | Sun  |                          |                      |                        |                  |                     |     |     |     |
| 8        | Mon  |                          | 200                  | 100                    | 200              | xx                  | X1  |     |     |
| 9        | Tue  | 100                      | 200                  | 100                    | 200              | xx                  |     | X1  |     |
| 10       | Wed  |                          | 200                  | 100                    | 200              | xx                  | X3  |     |     |
| 11       | Thur | 100                      | 200                  | 100                    | 200              | xx                  |     | X3  |     |
| 12       | Fri  |                          | 200                  | 100                    | 200              | xx                  | X5  |     |     |
| 13       | Sat  |                          |                      |                        |                  |                     |     | X5  |     |

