| 50 | Mon  | 30 | X19 |  |     | xx |  |  | X19 |
| 51 | Tue  |    | X19 |  | X19 | xx |  |  |     |
| 52 | Wed  |    |     |  | X19 | xx |  |  |     |
| 53 | Thur |    |     |  |     | xx |  |  |     |

Key: X1, X3 etc. refers to the day in which schoolchildren were first screened for schistosomiasis e.g., X1 screened on day 1 of the study calendar.

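### The Appendix 1 calendar contradicts the 21 ± 2 day window for the primary-endpoint visit: cohort X5 falls outside on any reading, and four more cohorts do if the window covers both stools

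*Protocol*

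**What the plan says.** The primary endpoint in Section 3.2 is "Cure rate at 21 days after treatment for the PZQ 60mg/Kg and PZQ 40mg/Kg groups". The visit that supplies it is headed "D21 (means 21 days after treatment +/- 2 days". Under that heading the protocol places the adverse-event questionnaire, haemoglobin and the parasitology: "Stool samples will be collected on two separate days and each day duplicate Kato Katz slides will be made for quantitative examination".

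Both stools enter the result. Section 7.1 says: "The measurement of egg count for each time point will be estimated as the mean of the 4 slides collected", meaning two slides from each of two samples.

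Section 6.2.2 adds that, at baseline and at follow-up, each child "will provide a stool specimen on two separate days at maximum interval of 5 days". It does not say how that interval relates to the D21 window.

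Section 3.2 refers to Appendix 1 for the schedule of activities. Its table, "Baseline Screening, Treatment and Safety Assessment Schedule", gives calendar days for screening, D0, D1, D21 and slide preparation. A cohort label such as X5 "refers to the day in which schoolchildren were first screened for schistosomiasis", so X5 was first screened on calendar day 5.

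The treatment visit has its own window: "D0 (means 7 days after baseline study +/-1 day".

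**The concern.** A visit window allows for slippage in the field. The calendar should aim at the target day and leave the tolerance for absent children and missed samples. Here the calendar itself uses up or exceeds the tolerance for most cohorts, so a team that follows Appendix 1 exactly will depart from Section 3.2.

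The affected samples decide the primary endpoint. The protocol does not say whether a stool taken after day 23 counts towards the D21 result. If that is settled only once data are in, the number of slides behind a cure classification could differ between cohorts for reasons unrelated to the children.

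**Working it through.** **Inputs.** D0 days come from the D0 column of Appendix 1. First D21 stool days come from the D21 column and the first entry in the slide column, and second stool days from the next entry in the slide column. The window is 21 − 2 = 19 to 21 + 2 = 23 days after treatment.

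**Planned number.** Section 3.2 expects 30% of 800 to qualify: 0.30 × 800 = 240. Appendix 1 shows eight cohorts of 30 at D21: 8 × 30 = 240. The two agree. The randomised target in Section 5 is 236, so the counts below are planning figures.

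**Days after treatment** = stool day − D0 day.

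| Cohort | D0 | First stool | Second stool | Days after treatment | First in 19–23? | Second in 19–23? |
|---|---|---|---|---|---|---|
| X1 | 8 | 31 | 32 | 23 / 24 | yes | no |
| X3 | 10 | 33 | 34 | 23 / 24 | yes | no |
| X5 | 12 | 36 | 37 | 24 / 25 | no | no |
| X9 | 15 | 38 | 39 | 23 / 24 | yes | no |
| X11 | 17 | 40 | 41 | 23 / 24 | yes | no |
| X15 | 22 | 43 | 44 | 21 / 22 | yes | yes |
| X17 | 24 | 45 | 46 | 21 / 22 | yes | yes |
| X19 | 29 | 50 | 51 | 21 / 22 | yes | yes |

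**Counts.**
- Whole visit outside the window: X5 only, 30 of 240 (12.5%). Its questionnaire and haemoglobin are on day 24 too.
- Second stool outside, if the window covers both stools: 5 × 30 = 150 of 240 (62.5%).
- If late stools were then excluded: X1, X3, X9 and X11, 4 × 30 = 120 children (50%), would keep two of four slides, and X5's 30 would keep none.

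**Screening to treatment**, against 7 ± 1 = 6 to 8 days, in the order X1, X3, X5, X9, X11, X15, X17, X19.
- From first screening (D0 day − label): 7, 7, 7, 6, 6, 7, 7, **10**.
- From the second baseline sample (calendar days 2, 4, 8, 10, 12, 16, 18, 22): 6, 6, **4**, **5**, **5**, 6, 6, 7.

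The first anchor puts X19 outside, and the second puts X5, X9 and X11 outside.

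**Check of the proposed D21 dates.**
- X5 on 33/34: 33 − 12 = 21 and 34 − 12 = 22.
- X1 on 30/31, X3 on 32/33, X9 on 37/38, X11 on 39/40: each gives 22 / 23.

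All are inside 19 to 23.

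**The case against.** The best defence is that the window fixes the visit and not each sample. Section 6.2.2 lets the two stools be up to five days apart, and Section 7.1 speaks of two samples within five days. The widest gap inside the window is 23 − 19 = 4 days, so an interval of five days could not fit. On that view X1, X3, X9 and X11 comply with a first contact on day 23. This stands as a possible reading, so a reader should not take 150 of 240 as settled. It does not rescue X5, whose first contact is already on day 24. Nor does the protocol state it: the D21 heading carries the window and both collections are listed under it.

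Three stronger inferences are tempting and not supported.

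- **That later stools defeat the reason for day 21.** Section 12.2 says the endpoint was timed to avoid eggs from worms immature at treatment. It gives no maturation time, and day 23 is already allowed. Nothing in the protocol shows that one or two more days matter.
- **That cure will be overstated because slides are missing.** No rule in the protocol discards late stools. If they are used, all four slides exist and nothing is lost.
- **That X19 is plainly treated too late.** Its ten days depend on counting from first screening. From its second baseline sample the interval is seven days. Section 3.2 also has a looser phrase, treatment within seven days (± 1). Read as an upper limit from the second sample, every cohort meets it. The conflict is with the D0 heading, and its cause is an undefined anchor.

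**Conclusion.** The calendar and the D21 window contradict each other. About 30 of 240 planned children (cohort X5) are outside on any reading, with the first contact one day late and the second stool two days late. About 150 of 240 are outside if the window covers both stools, which is the more natural reading of the D21 heading but not the only one.

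Randomisation is 1:1 in blocks of four, so the timing shift should fall on both arms alike, and no between-arm bias is claimed. The consequence is planned deviations on the primary endpoint, plus uncertainty about which slides count. Slides are lost only if out-of-window stools are excluded.

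Three cohorts are scheduled at days 21/22, so compliant dates were feasible. On the separate interval from screening to treatment, neither anchor tested makes every cohort satisfy the D0 heading. The result rests on the printed calendar days and the planned 30 children per cohort.

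**What to change.** Before the study starts, re-issue Appendix 1 as follows.

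- Move X5's entire D21 visit (questionnaire, haemoglobin and both stools) to calendar days 33/34, which are days 21/22 after treatment.
- Move the D21 visits of X1, X3, X9 and X11 one day earlier, to days 22/23 after treatment. Shift their microscopy entries to match.
- State in Section 3.2 that both D21 stool days must fall within 21 ± 2 days, and make the interval in Sections 6.2.2 and 7.1 subject to that.
- Define the event from which the seven days before D0 are counted, and reconcile Section 3.2, the D0 heading and Appendix 1. Which treatment timing is right is for the sponsor to settle.

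The cost is one re-issued table and a few sentences, with no extra visits or samples. There are small downsides. X1's D21 visit would share calendar day 30 with X19's D1 visit, and both need the physician. X3's second stool would share day 33 with X5's first: 60 children × 2 slides = 120 slides, below the 200 a day planned at baseline. Day 34 is a Saturday, but the calendar already uses it for slides. Four cohorts would still have their second stool on day 23, the last permitted day, so those dates leave no slack.

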#### 6M (means 180 days after treatment +/- 7 days)

At 6M follow up cure rate, egg reduction rate, weight and Hb will be determined in all study subjects in the trial. Therefore, stool samples will be collected on two separate days and each day duplicate Kato slides will be made for quantitative examination of *S mansoni* ova. This will allow cure rate and egg reduction rate at 6M to be calculated.

#### 12M (means 365 days after treatment +/- 14 days)

At this follow up activities conducted at 6M will be repeated, that is, cure rate, egg reduction rate, weight and Hb will be determined in all study subjects in the trial. Therefore, stool samples will be collected on two separate days and each day duplicate Kato slides will be made for quantitative examination of *S. mansoni* ova. This will allow cure rate and egg reduction rate at 12M to be calculated.

Table 1. A summary of study procedures are presented below for each visit:

|                               | Screening | Day 0 | Day1 | Day 21 | Month 6 | Month 12 |
|-------------------------------|-----------|-------|------|--------|---------|----------|
| Clinical history              | X         | X     |      |        |         |          |
| Inclusion/Exclusion criteria* | X         | X     |      |        |         |          |
| Cure rate                     |           |       |      | X      | X       | X        |
| Egg Reduction Rate            |           |       |      | X      | X       | X        |
| Adverse events                |           | X     | X    | X      |         |          |
| Weight                        |           | X     |      |        | X       | X        |
| Hb                            |           | X     |      | X      | X       | X        |

\* Screening for exclusion criteria includes urine test for pregnancy (childbearing age female participants) and diagnosis of *S. haematobium*.

### 3.3. Randomization:

Schoolchildren with *S. mansoni* and fulfilling both inclusion and exclusion criteria will be randomly assigned to two groups: one group will receive PZQ 40mg/kg and the other group PZQ 60mg/kg. Randomization will be generated in blocks of 4, in a ratio of 1:1 for each drug regimen. Sealed and numbered envelopes containing the treatment regimen for each sequential participant to be enrolled will be provided from TDR. The envelopes containing the codes will be kept in a locked cabinet and one designated person of the team will be responsible for them. This same person will be responsible for opening the envelope and verifying the corresponding treatment once a new participant is enrolled in the study. Each participant will be assigned a unique Study I.D. number (ID#). This ID# will be assigned in sequential order and will be recorded in the Screening Log. The treatment will be provided to the participant according to the Praziquantel regimen assigned by the randomization code and the participant's weight (Appendix 6). An electronic, password-protected copy of the randomization codes will be kept at TDR, Geneva.

The opened envelopes will be signed, dated, resealed and kept in the locked cabinet.

### 3.4. Blinding:

Blinding of the study will be achieved by ensuring that the person who calculates the dosage of PZQ to be given and provides the medication to the participants is not the person who evaluates safety. In addition those doing the parasitological analysis will not know the treatment given to the individual children.

## **4. SELECTION AND WITHDRAWAL OF PARTICIPANTS:**

The inclusion and exclusion criteria will be as follows:.

#### 4.1. Inclusion criteria

- Age 10-19 years
- Infected subjects with an egg excretion of  $\geq 100$  eggs per gram of faeces for *S. mansoni*.
- Those able and willing to be followed up
- Who have given written informed consent for stool, urine and blood samples. In case of adolescents (< 18 years), written informed consent from their parents and their verbal assent to be obtained.

Those who have satisfied the inclusion criteria will be further tested for the following exclusion criteria:

#### 4.2. Exclusion criteria

- Known previous history of adverse reactions associated with PZQ
- Pregnancy (by testing) or lactating
- Clinical malaria
- History of treatment in the past 30 days with PZQ
- Currently or in the past week using other medication that may affect the results of the present trial, as antibiotic
- Acute or chronic severe disease, including hepato-splenic schistosomiasis.
- Mixed *S. mansoni* and *S. haematobium* infections

The study will be carried out in a school setting and only children fulfilling the inclusion/exclusion criteria will be recruited for the study. Depending on the prevalence of infection on a specific school, it is expected that many children (usually at least half of them) won't fulfill all the criteria. The main reason for excluding children will be: because they do not have schistosomiasis or they don't have the required infection intensity of  $\geq 100$  eggs/g of stools for *S. mansoni*. As for all information obtained for the trial, the data will be kept confidential, and the reason why a child was not included in the study will not be released to the community. Teachers will be asked to assist the study team to deal with the problem of possible differentiation between those participating and not participating in the trial. All those infected but not included in the study will still be treated. The same will happen with pregnant girls. As stated before, they will be informed about their condition and counseled by the study nurse or physician, and referred to the Pre Natal assistance. However, this information will be kept confidential and only released to the person that it refers to.

#### 4.3. Subject withdrawal criteria

The study subject will be withdrawn from the trial if he/she presents any illness or condition that makes further participation impossible, or if he/she decides not to participate. The participant will be discontinued to participate in the study if during the follow-up period he/she takes an anti-schistosomal medication.

Withdrawn participants will not be replaced. Individual children will be free to withdraw from the study for whatever reason they chose.

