In Tanzania PZQ at 40mg/kg body weight as a single dose has been tested against infections by *S haematobium* (McMahon & Kolstrup, 1979) and *S mansoni* (Rugemalila et al., 1984). McMahon & Kolstrup (1979) recorded high cure rates of 83%, 76% and 71% against *S haematobium* at 1- month, 2- months and 6- months, respectively. In *S mansoni*, however, Rugemalila et al. (1984) observed lower cure rates of 35%, 56% and 63% at 1-month, 2- months and 6- months, respectively.

The unusually low cure rates reported by Stelma et al. (1995) in Senegal, while working in very intense focus of *S. mansoni*, has raised much concern about the emergency of resistance or tolerance of schistosomes to PZQ. So in order to circumvent this problem, several strategies to reduce the rate of schistosome species developing resistance against PZQ and to optimize the use of PZQ in schistosomiasis control has been suggested. In the present study, the suggested option to be explored is to increase the dose regimens of PZQ up to 60mg/kg body weight.

Stelma et al. (1997) increased the dose of PZQ from standard dosage of 40mg/kg to 60mg/kg and showed to have no significant improvement in efficacy. Van Lieshutt et al. (1994), however, showed that the opposite was true. This controversy requires to be urgently resolved by collecting data on the safety, efficacy and effectiveness of increased doses of PZQ in different epidemiological setting where schistosomiasis is highly endemic.

Children are especially vulnerable to schistosomiasis, and infected school-age children are often physically and intellectually compromised by concurrent anemia, attention deficits, learning disabilities, school absenteeism and higher dropout rates (Guyatt et al., 2001; WHO, 2002). Schistosomiasis Control Programs target school-aged children, aiming for clinical cure and morbidity reduction. Many previous trials were done with children and adolescents to test the efficacy of praziquantel alone or in combination with other drugs (Jaoko et al., 1996; Guisse et al., 1997; Olds et al., 1999; Urtzinger et al., 2000; de Clercq et al., 2002). Since praziquantel is a safe and well known drug (as described above) and the improvement of treatment should be achieved for those who need the most, children and adolescents will be the chosen study population for this trial.

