  - a) Egg reduction rate at 21 days after treatment for the PZQ 60mg/Kg and PZQ 40mg/Kg groups.
  - b) Comparison of frequency and severity of adverse events during the 4 hours after treatment, 24 hours and 21 days, for the PZQ 60mg/Kg and PZQ 40mg/Kg groups.
  - c) Comparison of the variation of hemoglobin (Hb) level at 21 days, 6 months and 12 months after treatment (as related to the baseline measurement), for the PZQ 60mg/Kg and PZQ 40mg/Kg groups.
  - d) Comparison of the variation of weight at 6 months and 12 months after treatment (as related to the baseline measurement), for the PZQ 60mg/Kg and PZQ 40mg/Kg groups.

The flow-chart below illustrates the study design:

[figure not shown]

Rapport with government and community leaders at district, ward, village and school levels will be established in the study area. Informed Consent will be obtained for each participant. For children considered minors written Informed Consent will be obtained from their guardians. Schoolchildren meeting the screening criteria will be recruited continuously, subjects will be examined quantitatively for *S mansoni* ova and semi-quantitatively for *S haematobium*. Two stool samples (2 Kato Katz slides will be prepared from each sample) and one urine sample will be collected within 5 days. Those who fulfill the inclusion and exclusion criteria for enrolment in the trial will be randomized to receive treatment with PZQ within 7 days (+/-1 day).

See Appendix 1 for the schedule of activities. It is estimated that 800 school children will be examined during the baseline study within one month. It is expected that about 240 children (30%) will fulfill the criteria for enrollment in the trial. Participants with positive *Schistosoma spp.* diagnosis who do not fulfill the inclusion and exclusion criteria will be treated with the standard treatment of a single dose of PZQ 40mg/Kg.

Schoolchildren in the treatment groups will be followed up for a total of 12 months post-treatment.

The following baseline screening and follow up visits will be done. As shown in Appendix 1 the baseline study is scheduled to last 23 days. Since enrollment is done continuously, activities of D0 will start on the 8th day after screening and activities of D1 on the 9th day and run concurrently with the screening.

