#### 5.2. Medications permitted and not permitted:

All medications except those with anti-schistosomal activity will be allowed during the trial. After the 21 days safety assessment, participants with diagnosis of intestinal helminths will be treated with mebendazole or albendazole. Those with anemia (as defined in section 6.2.4) will receive iron supplementation. If the participant has severe anemia he/she will be referred to appropriate health care.

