#### 7.2. Methods for assessing efficacy:

- Cure rate will be estimated as the proportion of subjects with negative result at 21 days after treatment.
- Egg reduction rate at 21 days after treatment will be estimated through the following formula:  
 $[1 - (\text{epg2} / \text{epg1}) \times 100]$  where epg1 and epg2 are the geometric mean of  $\log_{10}$  transformed (x+1) numbers of eggs per gram of faeces at the screening survey and the 21st day post-treatment survey.

The same calculations of cure rate and egg reduction rate will be estimated for the 6M and 12M follow-up in order to estimate reinfection rates.

7.3. Analysis: The cure rate and egg reduction rate will be compared between the 2 treatment regimens, PZQ 40mg/Kg and 60mg/Kg.

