## **11. ETHICAL CONSIDERATIONS FOR PROJECTS INVOLVING HUMAN SUBJECTS**

Research clearance for the proposed study has been obtained from the Medical Research Co-ordinating Committee of the National Institute for Medical Research, which acts as the National Ethics Committee in Tanzania and is attached.

At the beginning of the study meetings will be organized with parents and teachers of the earmarked schools, whereby detailed information will be provided by the research team about the aims, procedures, benefits and potential risks of the study.

Written informed consent will be obtained from all participants. In case of minors, the oral assent of the child will be asked, besides the written consent of the guardian. If the children is between 10-<14, and according to the Investigator's perception, he/she is not able to understand the information given during the informed consent procedure, the oral assent is not necessary.

Participation in the study will be on voluntary terms and that an individual will be free to withdraw from the study at any time. Withdrawal from the study will not affect ones statutory rights in any way.

All records of study subjects will be kept confidential.

All schoolchildren participating in the study and found to have schistosomiasis will be treated free of charge. Participants with schistosomiasis who do not fulfil the criteria for enrolment will be treated with the standard regimen of single dose Praziquantel at 40 mg/Kg.

Only parasitological specimens (Kato-Katz slides) will be kept for the duration of the study to allow for quality control and cross-checking. They will then be discarded. No other specimens will be kept.

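### Section 4.3 ends follow-up for any child who takes an anti-schistosomal drug, so later Hb and weight go uncollected, and unequally by arm if positive stools prompt the drug

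*Protocol*

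**What the plan says.** Section 4.3 of the protocol sets the rule: "The participant will be discontinued to participate in the study if during the follow-up period he/she takes an anti-schistosomal medication". The same section says that withdrawn children are not replaced. Section 5 gives each child a single dose, taken on day 0.

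Section 5.2 bears on how often the rule would apply: "All medications except those with anti-schistosomal activity will be allowed during the trial".

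The measurements at stake are in section 3.2. Change in Hb from baseline is a secondary endpoint at day 21, 6 months and 12 months (item c). Change in weight is one at 6 and 12 months (item d). The 6M visit text reads "At 6M follow up cure rate, egg reduction rate, weight and Hb will be determined in all study subjects in the trial", and the 12M text repeats that "cure rate, egg reduction rate, weight and Hb will be determined in all study subjects in the trial". Nothing visible provides for measuring a child after discontinuation.

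Two other places matter for interpretation. Section 7.2 says that cure rate and egg reduction rate "will be estimated for the 6M and 12M follow-up in order to estimate reinfection rates". Section 11 says "All schoolchildren participating in the study and found to have schistosomiasis will be treated free of charge", without saying when.

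**The concern.** The rule stops data collection because of something that happens after randomisation. For eggs the motive is easy to see: a second schistosomicide spoils any later reading of cure or reinfection. It does not follow that Hb and weight must stop too. They are separate endpoints, measured at visits already planned for every child.

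Two things are at stake for the 6- and 12-month Hb and weight comparisons. The sample shrinks with each child who takes such a drug. And if the drug is given because the stool is still positive, the children removed are treatment failures, which is the outcome the two doses are expected to change. Those still measured would then be selected by a result of the assigned dose, and the comparison would no longer be the randomised one. A later analysis plan can choose how to handle values taken after re-treatment, but it cannot create values that were never taken.

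**Working it through.** **1. What the rule stops.** The study drug is complete on day 0, so ending participation can only end visits and measurements. A child treated between D21 and 6M loses Hb and weight at both 6M and 12M. One treated after the 6M measurements loses only 12M. One treated after 12M loses nothing.

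**2. What it cannot touch.** Treatment prompted by eggs cannot come before the D21 stool. The primary cure rate, D21 egg reduction, D21 Hb and adverse events are therefore unaffected by it.

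**3. The plan's own figures.** Section 10.2 assumes cure rates of 60% v 80%, 80% power and 5% significance, and states 91 per group.
- Uncorrected, two-sided: n = [1.960√(2 × 0.70 × 0.30) + 0.842√(0.24 + 0.16)]² / 0.20² = 81.2, so 82.
- With continuity correction: (81.2/4) × [1 + √(1 + 4/(81.2 × 0.20))]² ≈ 91, as stated.
- 118 is 91 × 1.3 = 118.3. A 30% loss from 118 would leave 118 × 0.70 = 82.6. The point here does not depend on that difference.

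**4. Loss if D21 positives are treated.** Let f be the share of D21 positives who are then treated before 6M. The protocol gives no value, so f runs from 0 to 1. With p the cure rate:
- Lost per arm = 118 × f × (1 − p).
- Standard error ratio for a difference in mean Hb or weight change, assuming equal variances: √{[1/(1 − f(1 − p40)) + 1/(1 − f(1 − p60))] / 2}. The starting number cancels, so the ratio is the same from 118, 91 or 82.6 per arm.

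At the design rates, before other dropout:

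| f | Lost, 40 v 60 mg/kg | Left of 118 | Gap (points) | SE ratio |
|---|---|---|---|---|
| 0 | 0 v 0 | 118 v 118 | 0 | 1.000 |
| 25% | 11.8 v 5.9 | 106.2 v 112.1 | 5 | 1.040 |
| 50% | 23.6 v 11.8 | 94.4 v 106.2 | 10 | 1.087 |
| 75% | 35.4 v 17.7 | 82.6 v 100.3 | 15 | 1.141 |
| 100% | 47.2 v 23.6 | 70.8 v 94.4 | 20 | 1.208 |

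**5. Selection.** The share of D21 failures among children still followed is (1 − p)(1 − f) / (1 − f(1 − p)). It starts at 40% v 20%. At f = 50% it is 0.20/0.80 = 25% v 0.10/0.90 = 11%. At f = 100% it is zero in both arms.

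**6. Dependence on the cure rates, at f = 100%.** The ratio of losses is (1 − p40)/(1 − p60).
- 60% v 80%: 0.40/0.20 = 2.0.
- 60% v 70%: 0.40/0.30 = 1.33.
- 60% v 60%: 1.0. Loss is equal by arm, but the standard error still rises 29% (√(1/0.60) = 1.291).
- 35% v 55%: 0.65/0.45 = 1.44, with 76.7 v 53.1 of 118 lost and SE ratio √[(1/0.35 + 1/0.55)/2] = 1.529. The 35% is the 1-month figure that section 1 reports for 40 mg/kg, the one nearest D21; the 20-point gain is assumed. The 2- and 6-month figures in the same sentence are not D21 rates and are not used.

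**The case against.** The strongest reply is that section 4.3 only tidies up departures from section 5.2. These drugs are not allowed, no visit in section 3.2 or Table 1 treats a child who is positive at D21, 6M or 12M, and using the later egg results to estimate reinfection fits follow-up without re-treatment. On that reading few children are affected, and treatment unrelated to egg status, or prompted only by reinfection, would be about equal by arm. This stands. It makes the unequal loss conditional and the f = 100% row a ceiling.

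A reader might go further and take section 11's promise of free treatment to mean that D21 positives will be treated, so that unequal loss is built into the design. The text does not support that. The promise has no timing, most naturally refers to infection found at screening, and sits beside section 5.2, which points the other way. What can be said for the risk is less: section 4.3 anticipates such drug use, Appendix 1 has stools read within days of each D21 visit, and section 5.2 treats anaemia and other helminths after D21 but is silent on persisting schistosomiasis.

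A reader might also infer that a child still infected at 12M goes untreated. That is not supported either: section 11 sets no time limit and can cover that child. The flow-chart and consent pages are not shown, so all of this concerns the visible text only.

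The second reply is that removal isolates the effect of one assigned dose, whereas retention mixes in re-treatment. This stands in part. Let d be the difference in Hb or weight change between cured and uncured children (not given) and c the cure probability on re-treatment (assumed). The contrast acting through cure is then 0.20(1 − fc)d under retention. At f = 50% that is 0.14d for c = 0.6 and 0.10d for c = 1, against (0.80/0.90 − 0.60/0.80)d = 0.14d among children left under removal. So retention does not restore that contrast; it preserves the randomised groups and the sample. With the drug date recorded, later values can still be set aside by anyone who prefers the other question. Later Hb already reflects iron and deworming given after D21 under section 5.2, so it is not a pure effect of dose in any case.

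**Conclusion.** The point holds as an inexpensive improvement. For any child who takes an anti-schistosomal drug before 12M, section 4.3 ends collection of the remaining Hb and weight values, with no gain for those endpoints that could not be had by recording the drug.

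How many children this affects is unknown and may be few. Unequal loss needs a further assumption, that a positive D21 stool prompts treatment. Under it, at the design rates, the range runs from 12 v 6 of 118 and a 4% larger standard error (a quarter of positives treated) to a ceiling of 47 v 24 and 21% (all treated before 6M). If the cure rates are nearer the reported 1-month figure, the ceiling is higher (53% at 35% v 55%) but the ratio between arms is smaller. Equal cure rates, or treatment unrelated to egg status, give no arm difference, though the sample still shrinks.

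Only the 6- and 12-month Hb and weight comparisons are at issue. The D21 results are not affected by egg-prompted treatment, and unequal loss should not be described as expected.

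**What to change.** Amend section 4.3 so that:
- a child who takes an anti-schistosomal drug during follow-up stays in the scheduled 6M and 12M Hb and weight visits and is analysed in the randomised arm;
- the drug, dose and date are recorded;
- later egg results from that child are handled separately;
- discontinuation is reserved for withdrawn consent or inability to continue.

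The cost is a short amendment and one extra record per affected child. No visits are added, because 6M and 12M are already scheduled for everyone, and if nobody takes such a drug nothing changes. The small downside is that 6M and 12M Hb and weight would include the effect of any re-treatment, which the recorded date allows an analysis to examine.
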